## 8.4 Exposure

The exposure information including dose level (ie, SD [only for analysis set based on Dose1 SD], LD/SD, SD/SD), number of dose(s), all available dose schedule for two doses and further categorized dose schedule (< 6 weeks, 6-8 weeks, 9-11 weeks, 12+ weeks) will be summarized by treatment for overall and each study. The summary will be performed for Any Dose for Safety analysis set, Any Dose for Efficacy analysis set, Dose1 SD for Safety analysis set, Dose 1 SD Seronegative for Efficacy analysis set, SDSD + LDSD Seronegative for Efficacy analysis set, SDSD + LDSD for Immunogenicity analysis set, and SDSD for Immunogenicity by actual treatment. The categories for dose schedule may be combined if number of participants are small in some of categories.

A listing of exposure will be provided at the time of the primary analysis.

## 9. EFFICACY EVALUATIONS

### 9.1 Efficacy Assessments

Efficacy analysis will be assessed at time planned in Section 4.1. The planned 5% alpha will be split across the interim and primary analyses as described in Section 4.1.

All data from participants with SARS-CoV-2 virologically positive results from RT-PCR or other nucleic acid amplification tests will be assessed by a blinded adjudication committee and the adjudicated endpoints used for all analyses. WHO clinical progression scale ([WHO et al 2020](#)) will be utilized to assess the severity of disease. The description of WHO clinical progression scale is in [Table 2](#).

The case for evaluation of efficacy based on adjudicated results are defined as in [Table 6](#).

The overview of the endpoints and corresponding analysis populations is shown in the [Appendix A](#).

**Table 6 Case Definitions for Evaluation of Efficacy**

| Case                                                                                     | Definition                                                                                                                                                                                              |
|------------------------------------------------------------------------------------------|---------------------------------------------------------------------------------------------------------------------------------------------------------------------------------------------------------|
| COVID-19 (Primary)
Virologically-confirmed a symptomatic cases of COVID-19 | PCR-confirmed SARS-CoV-2 and at least one of the following symptoms: objective fever (defined as $\geq 37.8$ °C), cough, shortness of breath, anosmia, or ageusia. Confirmed by adjudication committee. |
| COVID-19 Severe Disease                                                                  | WHO grade $\geq 6^b$                                                                                                                                                                                    |
| COVID-19 Hospital Admission                                                              | WHO grade $\geq 4^b$                                                                                                                                                                                    |
| COVID-19 Requiring ICU                                                                   | WHO grade $\geq 7^b$                                                                                                                                                                                    |
| COVID-19 Death                                                                           | WHO grade = $10^b$                                                                                                                                                                                      |
| Asymptomatic SARS-CoV-2 infection                                                        | PCR-confirmed SARS-CoV-2 infection and no symptom recorded in data. Confirmed by adjudication committee.                                                                                                |

a Virologically-confirmed from RT-PCR or other nucleic acid amplification test.

b WHO clinical progression scale.

### 9.1.1 Primary Efficacy Endpoint

Incidence of SARS-CoV-2 Virologically-confirmed COVID-19 Occurring  $\geq 15$  Days Post Second Dose of Study Intervention

The primary efficacy endpoint is the first case of SARS-CoV-2 virologically-confirmed COVID-19 occurring  $\geq 15$  days post second dose of study intervention. The case is defined as COVID-19 (primary) in [Table 6](#). Only cases with both the sampling date of positive PCR test and COVID-19 symptom(s) onset date  $\geq 15$  days post second dose will be counted as events. The event date is the date of the PCR test date or date of symptom onset, whichever comes first, and this date will be defined by the endpoint review committee for analysis. For participants with multiple events, only the first occurrence will be used for the primary efficacy endpoint analysis.

The primary efficacy analysis will be based on SDSD + LDSD Seronegative for Efficacy analysis set.

Period at risk for primary endpoint for pooled analysis will be calculated using the reference start as the second dose date + 15 days as Day 1. Calculations for Period at risk are provided below:

Period at risk for primary endpoint = [Last date at risk – (the second dose date + 15 days)] + 1

Where last date at risk will be:

- Date of first event for those diagnosed with SARS-CoV-2 virologically-confirmed COVID-19;
- Date of completion/early discontinuation for participants who complete or discontinue study without event;
- Data cut-off date for analysis for rest of participants who are ongoing without event at the time of analysis.

If the primary endpoint is missing, the period at risk for primary endpoint will be set to missing.

#### **9.1.1.1 Time to Events Endpoints for Supplementary Analysis**

Time to First SARS-CoV-2 Virologically-confirmed COVID-19 Occurring  $\geq 15$  Days Post Second Dose of Study Intervention

Time to First SARS-CoV-2 Virologically-confirmed COVID-19 is defined as the time from the second vaccination + 15 days until the date of the first SARS-CoV-2 virologically-confirmed COVID-19. The calculation is same as the period at risk for the primary endpoint for the pooled analysis. Participants with SARS-CoV-2 virologically-confirmed COVID-19 will be counted as having event while the participants with non-missing value for the period at risk for primary endpoint for pooled analysis will be counted as censored.

Participants with missing value for the period at risk for primary endpoint for pooled analysis will be excluded from analysis.

### **9.1.2 Secondary Efficacy Endpoints**

#### **9.1.2.1 Incidence of Severe COVID-19 Occurring $\geq 15$ Days Post Second Dose of Study Intervention**

An event is defined as COVID-19 Severe Disease in [Table 6](#), and both the sampling date of positive PCR test and COVID-19 symptom(s) onset date  $\geq 15$  days post second dose. For participants with multiple events, only the first occurrence will be used for analysis.

#### **9.1.2.2 Incidence of Severe COVID-19 Occurring Post First Dose of Study Intervention**

An event is defined as COVID-19 Severe Disease in [Table 6](#), and both the sampling date of positive PCR test and COVID-19 symptom(s) onset date post first dose. For participants with multiple events, only the first occurrence will be used for analysis.

#### **9.1.2.3 Incidence of Severe COVID-19 Occurring $\geq$ 22 Days Post First Dose of Study Intervention**

An event is defined as COVID-19 Severe Disease in [Table 6](#), and both the sampling date of positive PCR test and COVID-19 symptom(s) onset date  $\geq$  22 days post first dose. For participants with multiple events, only the first occurrence will be used for analysis.

#### **9.1.2.4 Incidence of Asymptomatic SARS-CoV-2 Infection Occurring $\geq$ 15 Days Post Second Dose of Study Intervention for COV002 Only**

An event is defined as Asymptomatic SARS-CoV-2 infection in [Table 6](#) and a PCR-positive sample collected  $\geq$  15 days post second dose. For participants with multiple events, only the first occurrence will be used for analysis.

The period at risk for SARS-CoV-2 Virologically-confirmed COVID-19 will be calculated similarly to period at risk for the primary endpoint for the pooled analysis replacing information related the primary endpoint for the pooled analysis with information of Asymptomatic SARS-CoV-2 Infection.

The corresponding time to event endpoint is below:

- Time to First Asymptomatic SARS-CoV-2 Infection Occurring  $\geq$  15 Days Post Second Dose of Study Intervention for COV002 only

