ECMO = extracorporeal membrane oxygenation; FiO2 = fraction of inspired oxygen; NIV = non-invasive ventilation; pO2 = partial pressure of oxygen; SpO2 = oxygen saturation.

Source: (WHO et al 2020).

Case definitions for the pooled analysis are given in Table 6. Per protocol in UK studies ICU admission was a protocol defined endpoint. In order to standardise “ICU admission” across trials for differences in local medical practice, this was redefined as “Requiring ICU admission” and corresponds to those WHO severity grades reflecting the need for mechanical ventilation.

Studies COV001, COV002, COV003, and COV005 are all randomised, controlled studies in healthy volunteers with similar efficacy endpoints. Case detection methods for efficacy assessments are also similar. Access to care for passive case detection is available in all studies; COV002 also includes weekly self-swabs for detection of infection and COV005 includes nasal swab and/or saliva on each scheduled visit. Key inclusion criteria are similar for all studies, except for age. Although there are some differences in the exclusion criteria across the studies, study populations are generally similar. All studies excluded patients with serious conditions or receiving medication that could interfere with the study conduct or the interpretation of study data.

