#### **9.1.2.5 Incidence of Asymptomatic SARS-CoV-2 Infection Occurring $\geq$ 22 Days Post First Dose of Study Intervention for COV002 Only**

This endpoint will be calculated in the same manner as asymptomatic SARS-CoV-2 infection confirmed by RT-PCR COVID-19 occurring  $\geq$  15 days post second dose of study intervention for COV002 only (Section [9.1.2.4](#)) by changing the reference date from date of 15 Days post second dose to date of 22 days post first dose and the analysis set will follow [Appendix A](#).

The corresponding time to event endpoint is below:

- Time to Asymptomatic SARS-CoV-2 Infection Confirmed by RT-PCR COVID-19 Occurring  $\geq$  22 Days Post First Dose of Study Intervention for COV002 only

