### **9.2.2 Secondary Efficacy Analyses**

#### **9.2.2.1 Incidence of Asymptomatic SARS-CoV-2 Infection COV002 only**

The analysis for those endpoints will be conducted in a similar manner as described in Section 9.2.1.1 (see Pooled Analysis of Primary Efficacy Endpoint) but remove Study code from model.

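### COV002 asymptomatic-infection endpoints count time after swabbing stops as infection-free, which understates incidence and biases vaccine efficacy, in an unknown direction, if swab coverage differs between arms

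*SAP*

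**What the plan says.** Table 6 of the SAP defines the asymptomatic case as "PCR-confirmed SARS-CoV-2 infection and no symptom recorded in data", confirmed by adjudication. Section 4 describes passive case detection in all four studies and adds that "COV002 also includes weekly self-swabs for detection of infection".

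Section 9.1.2.4 does not write out a period at risk for this endpoint. It takes the primary endpoint's period, "replacing information related the primary endpoint for the pooled analysis with information of Asymptomatic SARS-CoV-2 Infection". Section 9.1.2.5 repeats the calculation "by changing the reference date from date of 15 Days post second dose to date of 22 days post first dose". Each section also lists a matching time-to-event endpoint.

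The borrowed rule is in Section 9.1.1. The last date at risk is one of three:

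- the date of the first event;
- the day on which someone with no event finishes the study or leaves it early;
- "Data cut-off date for analysis for rest of participants who are ongoing without event at the time of analysis".

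On the model, Section 9.2.2.1 states: "The analysis for those endpoints will be conducted in a similar manner as described in Section 9.2.1.1", dropping only the study term. The Section 9.2.1.1 model uses the logarithm of the period at risk as its offset.

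**The concern.** The Section 9.1.1 rule suits symptomatic disease. A participant who falls ill can still be picked up by passive surveillance up to the cut-off, so on-study time is observed time.

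That does not carry over to an infection without symptoms, which is seen only if a well person is sampled. A COV002 participant who stops self-swabbing but stays in the study has little or no chance of recording this event, yet keeps adding event-free person-time until cut-off. The rate in that arm is then too low. If swabbing falls off more in one arm than the other, the difference in sampling passes into the VE estimate, and the SAP plans no output that would let a reader see it.

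**Working it through.** The SAP states no event count, power or swab-coverage figure for these endpoints, so there is no plan figure to reproduce. The check has two parts.

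**1. Does any other rule remove the unswabbed time?**

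- Section 9.1.2.4 substitutes the event information. It does not add a last-swab date or any other end of observation.
- Participants who leave the study are censored at discontinuation. The problem therefore concerns those who stay in the study and stop swabbing.
- Section 9.1.1 says: "If the primary endpoint is missing, the period at risk for primary endpoint will be set to missing". This is not tied to swabbing, and it removes a whole period rather than shortening a partly observed one.
- Section 7.4 leaves missing values unimputed in general and has no rule for missed swabs.
- No section plans a summary of swab adherence or a sensitivity analysis for it.

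Nothing else in the SAP corrects the rule.

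**2. How far could VE move?**

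Let fV and fC be the shares of counted time actually covered by swabs in the AZD1222 and control arms. With a constant hazard λ, follow-up T and rare events, expected events per participant are about λ × f × T and counted person-time is about T, so the estimated rate is about λ × f. Hence

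apparent RR ≈ true RR × fV / fC, and apparent VE ≈ 1 − (1 − true VE) × fV / fC.

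The coverages below are assumptions.

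| AZD1222 / control coverage | fV / fC | Apparent VE, true VE 0% | Apparent VE, true VE 30% |
|---|---|---|---|
| 80% / 80% | 1.000 | 0% | 30% |
| 70% / 80% | 0.875 | 12.5% | 1 − 0.7 × 0.875 = 38.75% |
| 60% / 80% | 0.750 | 25% | 1 − 0.7 × 0.750 = 47.5% |
| 80% / 70% | 1.143 | −14.3% | 1 − 0.7 × 1.143 = 20% |

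In the first row VE is untouched, but each arm's rate is 80% of its true value.

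The approximation was compared with exact exponential rates, assuming a control hazard of 0.03 per follow-up period. Events per participant are 1 − exp(−λfT). Counted person-time is [1 − exp(−λfT)]/λ + exp(−λfT) × (1 − f) × T.

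| Coverage | True VE | Approximate | Exact, SAP rule | Exact, time ended at last swab |
|---|---|---|---|---|
| 80% / 90% | 0% | 11.1% | 11.0% | 0.0% |
| 70% / 90% | 0% | 22.2% | 22.1% | 0.0% |
| 90% / 70% | 0% | −28.6% | −28.3% | 0.0% |
| 70% / 90% | 30% | 45.6% | 45.5% | 30.0% |
| 90% / 70% | 30% | 10.0% | 10.2% | 30.0% |

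The last column drops the second term of person-time, so the rate equals λ whatever f is. It holds only if stopping is unrelated to infection risk.

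**The case against.** The strongest reply is that the SAP gives no evidence of swab drop-off, let alone unequal drop-off. How long swabs continue and how missed ones are chased may be settled in the COV002 protocol. Participants are blinded and the COV002 control is an active vaccine, MenACWY, so differences of 10 to 20 percentage points are speculative, and equal drop-off leaves VE unchanged. This stands as a limit on size. It does not answer the defect, because the SAP itself fixes the period-at-risk rule.

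A reader might go further than the text allows in three ways:

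- **That the self-swab is the only way to find a case.** Table 6 and Section 9.1.2.4 do not restrict the source of the positive sample, and Section 9.1 sends all participants with positive RT-PCR or other nucleic acid results to adjudication. Table 1 says COV002 gives priority to health professionals and highly exposed adults, so positives from other testing are not excluded. What the SAP supports is that weekly swabs are the only routine sampling of well participants it describes.
- **That swabbing is voluntary.** The SAP does not say so.
- **That uneven drop-off would appear as efficacy.** It would do so only if the AZD1222 arm swabs less. If the control arm swabs less, VE is understated.

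A simple cut at the last self-swab would also be open to fair criticism. It could discard later genuine positives from other tests, it leaves earlier gaps counted as observed, and it can give a non-positive period whose logarithm is undefined. These points are taken into the fix.

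**Conclusion.** The point holds for Sections 9.1.2.4 and 9.1.2.5. The period at risk does not match the time in which the event can be routinely observed, and no other rule in the SAP compensates. Drop-off understates the incidence rate in each arm where it occurs. VE is biased only if coverage differs between arms, roughly in proportion to the ratio of coverages, in a direction and by an amount that the SAP does not allow anyone to determine. The range from −14% to 25% for a vaccine with no effect, in the first table, illustrates assumed coverages of 60% to 80%; it is not an estimate.

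A reader might infer that the main efficacy result is in doubt. It is not: these are single-study secondary endpoints, listed as exploratory for COV002 in Table 1, and the alpha split and analysis triggers in Section 4.1 concern symptomatic disease. This is a cheap improvement that should be made.

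**What to change.** In Sections 9.1.2.4 and 9.1.2.5, for these endpoints only:

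1. Define the last date at risk as the earliest of the first event, the last sample with a valid PCR result, study completion or discontinuation, and data cut-off. Count self-swabs and any other PCR or nucleic acid result accepted for adjudication, so that later genuine positives are kept. Use this period for both the offset and the censoring.
2. Exclude participants with no valid sample on or after the start of the risk period, since their log offset would be undefined, and report their number by arm.
3. Report swab coverage by arm, including gaps between swabs, which a last-sample rule does not remove.
4. Keep the present cut-off rule as a sensitivity analysis.
5. State the assumption that stopping swabs is unrelated to infection risk.
6. Correct the sentence in Section 9.1.2.4 that introduces the period at risk. It names virologically confirmed COVID-19 where asymptomatic infection is meant.

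The cost is SAP wording, a merge of dated swab results including negatives, and somewhat less person-time. The SAP does not say whether those dated results are already in the pooled data, so that needs confirming.

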#### **9.1.2.5 Incidence of Asymptomatic SARS-CoV-2 Infection Occurring $\geq$ 22 Days Post First Dose of Study Intervention for COV002 Only**

This endpoint will be calculated in the same manner as asymptomatic SARS-CoV-2 infection confirmed by RT-PCR COVID-19 occurring  $\geq$  15 days post second dose of study intervention for COV002 only (Section [9.1.2.4](#)) by changing the reference date from date of 15 Days post second dose to date of 22 days post first dose and the analysis set will follow [Appendix A](#).

The corresponding time to event endpoint is below:

- Time to Asymptomatic SARS-CoV-2 Infection Confirmed by RT-PCR COVID-19 Occurring  $\geq$  22 Days Post First Dose of Study Intervention for COV002 only

#### **9.1.2.6 Incidence of SARS-CoV-2 Virologically-confirmed COVID-19 Occurring Post First Dose of Study Intervention**

This endpoint will be calculated in the same manner as primary endpoint (Section [9.1.1](#)) by changing the reference date from date of 15 Days post second dose to the first dose date and the analysis will be performed on Any dose for efficacy analysis set.

The corresponding time to event endpoint is below:

- Time to First SARS-CoV-2 Virologically-confirmed COVID-19 Occurring Post First Dose of Study Intervention

#### **9.1.2.7 Incidence of SARS-CoV-2 Virologically-confirmed COVID-19 Occurring 22 Days Post First Dose of Study Intervention**

This endpoint will be calculated in the same manner as primary endpoint (Section 9.1.2.1) by changing the reference date from date of 15 Days post second dose to date of 22 days post first dose and the analysis will be performed on Dose1 SD for efficacy analysis set.

The corresponding time to event endpoint is below:

- Time to First SARS-CoV-2 Virologically-confirmed COVID-19 Occurring 22 Days Post First Dose of Study Intervention

#### **9.1.2.8 Duration of Follow-up**

For participants in the pooled analysis, the duration of follow-up since the first dose, 22 days post the first dose and 15 days post the second dose will be calculated respectively as study completion/discontinuation date - reference date +1. If subject did not discontinue from the study at the time of the analysis, the data cut-off date will be used. The duration will be summarized by treatment group.

#### **9.1.2.9 Incidence of COVID-19 Hospital Admission Occurring $\geq 15$ Days Post Second Dose of Study Intervention**

An event is defined as COVID-19 Hospital Admission in Table 6 and with both admission date of hospitalization and onset date of associated COVID-19 are  $\geq 15$  days post second dose of study intervention.

#### **9.1.2.10 Incidence of COVID-19 Hospital Admission Occurring Post First Dose of Study Intervention**

An event is defined as COVID-19 Hospital Admission in Table 6 and with both admission date of hospitalization and onset date of associated COVID-19 are post first dose of study intervention.

#### **9.1.2.11 Incidence of COVID-19 Hospital Admission Occurring 22 Days Post First Dose of Study Intervention**

An event is defined as COVID-19 Hospital Admission in Table 6 and with admission date of hospitalization and onset date of associated COVID-19 are  $\geq 22$  days post first dose of study intervention.

**9.1.2.12 Incidence of COVID-19 Death Occurring  $\geq$  15 Days Post Second Dose of Study Intervention**

An event is defined as COVID-19 Death in [Table 6](#) and both death date and onset date of associated COVID-19 are  $\geq$  15 days post second dose of study intervention.

**9.1.2.13 Incidence of COVID-19 Death Associated with SARS-CoV-2 Virologically-confirmed COVID-19 Occurring Post First Dose of Study Intervention**

An event is defined as COVID-19 Death in [Table 6](#) and with both death date and onset date of associated COVID-19 are post first dose of study intervention.

**9.1.2.14 Incidence of COVID-19 Death Associated with SARS-CoV-2 Virologically-confirmed COVID-19 Occurring 22 Days Post First Dose of Study Intervention**

An event is defined as COVID-19 Death in [Table 6](#) and with both death date and onset date of associated COVID-19 are  $\geq$  22 days post first dose of study intervention.

**9.1.2.15 Incidence of COVID-19 Requiring ICU Occurring  $\geq$  15 Days Post Second Dose of Study Intervention**

An event is defined as COVID-19 Requiring ICU in [Table 6](#) and with both admission date and onset date of associated COVID-19 are  $\geq$  15 days post second dose of study intervention.

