**Table 2 WHO Clinical Progression Scale**

| Patient State                  | Descriptor                                                                                                                 | Score |
|--------------------------------|----------------------------------------------------------------------------------------------------------------------------|-------|
| Uninfected                     | Uninfected; no viral RNA detected                                                                                          | 0     |
| Ambulatory mild disease        | Asymptomatic; viral RNA detected                                                                                           | 1     |
|                                | Symptomatic; independent                                                                                                   | 2     |
|                                | Symptomatic; assistance needed                                                                                             | 3     |
| Hospitalised: moderate disease | Hospitalised; no oxygen therapy a                                                                               | 4     |
|                                | Hospitalised; oxygen by mask or nasal prong                                                                                | 5     |
| Hospitalised: severe disease   | Hospitalised; oxygen by NIV or high flow                                                                                   | 6     |
|                                | Intubation and mechanical ventilation, pO 2 /FiO 2 ≥ 150 or SpO 2 /FiO 2 ≥ 200 | 7     |
|                                | Mechanical ventilation pO 2 /FiO 2 < 150 (SpO 2 /FiO 2 < 200) or vasopressors  | 8     |
|                                | Mechanical ventilation pO 2 /FiO 2 < 150 and vasopressors, dialysis, or ECMO                         | 9     |
| Dead                           | Dead                                                                                                                       | 10    |

a If hospitalised for isolation only, record status as for ambulatory patient.

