**9.1.2.16 Incidence of COVID-19 Requiring ICU Occurring Post First Dose of Study Intervention**

An event is defined as COVID-19 Requiring ICU in [Table 6](#) and with both admission date and onset date of associated COVID-19 are post first dose of study intervention.

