### **9.2.2.3 Other Secondary Efficacy Endpoints**

The remaining endpoints will be analysed in the same manner as the pooled analysis of the primary efficacy endpoint as described in Section 9.2.1.1 (see Pooled Analysis of Primary Efficacy Endpoint). VE will not be computed unless 5 cases have accrued for the respective endpoint, but the distribution by groups will be presented.

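### The Requiring ICU endpoint is defined by WHO grade alone, but its event rule adds an unspecified admission date that can drop cases meeting the definition

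*SAP*

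**What the plan says.** Section 4 of the SAP, in the text below Table 2, explains that ICU admission was an endpoint in the UK protocols. It was recast for the pooled analysis as requiring ICU, in order to standardise it "across trials for differences in local medical practice". The recast endpoint "corresponds to those WHO severity grades reflecting the need for mechanical ventilation". Table 6 carries this out: the case is WHO grade 7 or above, which includes grade 10 (dead), with no admission criterion.

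The event rules add a condition. Section 9.1.2.15 asks for the Table 6 case and "with both admission date and onset date of associated COVID-19 are" at least 15 days after the second dose. Section 9.1.2.16 has the same condition for the period after the first dose ("with both admission date and onset date of associated COVID-19 are post first dose of study intervention"), and section 9.1.2.17 has it from day 22 after the first dose.

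The hospital endpoints (sections 9.1.2.9 to 9.1.2.11) also need an admission date, but there the kind is named: "with both admission date of hospitalization and onset date of associated COVID-19 are". Severe disease (grade 6 or above, sections 9.1.2.1 to 9.1.2.3) is dated by PCR sample and symptom onset. COVID-19 death (sections 9.1.2.12 to 9.1.2.14) is dated by death and onset. Neither needs an admission.

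Section 9.2.2.3 says "VE will not be computed unless 5 cases have accrued for the respective endpoint"; below that number the distribution by group is still shown.

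**The concern.** The definition and the event rule use different criteria. The definition takes local care decisions out of the endpoint. The rule makes an event depend on an admission having taken place and been dated. The two conditions must both hold, so a grade 7 or higher case without that date cannot be an event, however severe it was.

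The wording is also open. Two programmers could read *admission date* as ICU admission or as hospital admission, and derive different event sets from the same adjudicated data. At stake are three secondary endpoints with few expected cases, for which a fixed minimum count decides whether VE is reported at all.

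**Working it through.** The SAP gives no figure for this point, so the check is to pass each type of grade 6 to 10 case through the rules under both readings.

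**Inputs.** Table 2 places grades 6 to 9 under "Hospitalised: severe disease", while grade 10 is a separate state with no hospital condition. Table 6 gives the cut-offs. Sections 9.1.2.1 to 9.1.2.3 and 9.1.2.15 to 9.1.2.17 give the date rules. Section 7.4 does not impute missing values unless a rule says so, and its rules cover adverse-event dates only.

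**Comparison**, assuming that every date that exists lies in the window:

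| Case | Meets Table 6, Requiring ICU | Event if ICU admission is meant | Event if hospital admission is meant | Event for severe disease |
|---|---|---|---|---|
| Grade 6 | no | no | no | yes |
| Grade 7–9, in an ICU | yes | yes | yes | yes |
| Grade 7–9, outside an ICU | yes | **no** | yes | yes |
| Grade 10, had been in an ICU | yes | yes | yes | yes |
| Grade 10, in hospital but never in an ICU | yes | **no** | yes | yes |
| Grade 10, never admitted | yes | **no** | **no** | yes |

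The ICU reading loses three types of case and the hospital reading loses one. Under both readings, a death without any admission meets Table 6 and is not an event.

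**Which reading is meant.** The ICU reading is the more natural. The hospital sections qualify the term ("both admission date of hospitalization and onset date of associated COVID-19") and the ICU sections do not, and the source endpoint was ICU admission. The text does not settle it. Table 1 lists ICU admission as an endpoint for COV001 and COV002 but not for COV003 or COV005, so the SAP gives no assurance that an ICU date is held for the last two.

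**Effect on the 5-case minimum.** Let N be the number of Table 6 cases in the window and k the number without the required date. VE is lost when N ≥ 5 but N − k < 5, that is, when 5 ≤ N ≤ 4 + k. Both numbers are assumptions:

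- k = 0: no effect.
- k = 1: VE is lost only if N = 5 (5 − 1 = 4).
- k = 2: VE is lost if N = 5 or 6 (5 − 2 = 3; 6 − 2 = 4).
- N of 7 or more with k of at most 2: VE is still computed (7 − 2 = 5), but on fewer cases than Table 6 defines.

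**The case against.** The strongest reply is that the admission is to hospital. Table 2 treats every ventilated participant as hospitalised, so none is lost, and only a death outside hospital falls through. Section 4 ties the endpoint to ventilation, and a death without ventilation does not clearly show that need, so leaving it out could be deliberate. This narrows the point but does not remove it. The SAP does not say that hospital admission is meant, and Table 6 includes grade 10 without qualification.

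A reader might infer that unequal ICU access in the UK, Brazil and South Africa would bias the pooled result. The SAP does not support this. It speaks of differences in practice, not access, and section 4 says that access to health care is good for all participants.

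A reader might also infer that the severity endpoints are meant to nest and that the rule breaks this. The SAP never says that they form a gradient. Nor are deaths hidden: they count under COVID-19 death and severe disease when those date rules are met.

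Finally, one might call the hospital-admission rule an error of the same kind. An admission date is a reasonable demand for an endpoint named hospital admission. What remains is that Table 6 (grade 4 or above, which includes death) and the date rule disagree on a death without admission.

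**Conclusion.** The point holds for sections 9.1.2.15 to 9.1.2.17. The event rule adds a condition that conflicts with the SAP's own definition and with the stated reason for it, and no other section rescues a case without the date. The certain part is narrow: a grade 10 case with no admission of any kind is excluded under either reading. It would go too far to say that ventilated cases are lost, because that depends on the ICU reading.

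The SAP does not allow the number of affected cases to be derived; it may be small or zero. The consequence is concrete only near the 5-case minimum, where one lost case can replace a VE estimate with counts by group. The split alpha in section 4.1 is assigned to the interim and primary analyses, and no success criterion is set for these endpoints, so no claim about lost significance is made. The point deserves correction but does not touch the primary analysis.

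**What to change.** In sections 9.1.2.15 to 9.1.2.17, delete the admission-date condition. Define the event as adjudicated WHO grade 7 or above with both PCR sampling date and symptom-onset date in the window, as sections 9.1.2.1 to 9.1.2.3 already do for severe disease. Report actual ICU admissions as a descriptive row.

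In sections 9.1.2.9 to 9.1.2.11, state whether a COVID-19 death without hospital admission counts, and align Table 6 with the answer. Either choice is defensible.

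The cost is SAP wording and a small change in derivation. It uses adjudicated grades and dates already needed for severe disease, so no new data are required. There are two downsides. The endpoint no longer records actual ICU admission, which is why the descriptive row is needed. The PCR date also becomes a condition that the present ICU rule lacks, so the programmer should list any case whose status changes for that reason.
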